#### Secondary outcome measures

A variety of secondary outcome measures will also be gathered. Social and academic functioning will be assessed by various measures. While social functioning measures include *social competence* and involvement in *social activities* with peers, academic functioning will be assessed using the measure of *cognitive competence*, and *grades* provided by the school. Perceived cognitive and social competence will be measured using slightly modified subscales from Harter’s [46] Self-perception Profile for Children [47]. In addition to *self*- *and school*-*related absence*, *intentions to quit school*, 4-item scale developed by Studsrød & Bru [48] will also be measured. *Social anxiety* will be assessed using the adapted version of the Hopkins Symptom Checklist (SCL-10) anxiety items [49]. *Reactive aggression* will be measured using an adapted version of Roland and Idsoe’s reactive aggression scale [50].

#### Mediators

The frequency of *negative thoughts* will be assessed using the single-factor, short-form version of the Automatic Thoughts Questionnaire (ATQ; [51, 52]). It has been suggested that this short version of ATQ shows high reliability and validity, without deteriorating content domain coverage of the construct [52]. The intensity of *dysfunctional attitudes* will be measured with the revised version of the Dysfunctional Attitude Scale (DAS; [53]) which is one of the most commonly used instruments as a mediator of outcome in CBT for depression [54]. Two-factor solution with 17 items, consisting of ‘dependency’ and ‘perfectionism/performance evaluation’, demonstrated good reliability and convergent construct validity [53]. Revised version of the Ruminative Responses Scale (RRS;[55, 56]), a self-report measure of *rumination* with 10 items, will be used to measure two aspects of rumination, reflecting and brooding. This version of RRS does not include items that seem to overlap with the measures of depressive symptoms [56]. *Emotion regulation strategies* will be assessed through the Norwegian version of the Emotion Regulation Questionnaire (ERQ; [57, 58]). The ERQ is a 10-item measure that assesses the use of two common emotion regulation strategies: cognitive reappraisal and expressive suppression.

#### Moderators

Research in Norway show higher prevalence of mental health problems among young people of immigrant origin compared to native peers throughout elementary, secondary and high school years [17]. Therefore, we will also explore whether *immigrant status* moderates the effect of the intervention. Adolescents will be asked to provide information about themselves, their parents and grandparents to evaluate their immigrant status and generation in detail.

The moderating role of *stressful life events* will also be assessed using the adapted version of the established life event lists for young people [59, 60]. The checklist consists of 10 pleasant or unpleasant events that an adolescent may have experienced in the past six months.

Course leaders will be asked about fidelity and attitudes, and how they provide the intervention retrospectively.

### Sample size and power calculations

Because the design is a single-centre cluster-randomized effectiveness trial with active control, where groups rather than individuals are randomized, possible cluster effects must be accounted for when calculating appropriate sample size [61]. We approximated cluster effects influencing our main outcome (depressive symptoms) by taking advantage of data from the existent study on ACDC [37], and calculated intraclass correlations (ICC’s) with the course groups as cluster. ICC for depressive symptoms was .08. Our calculations showed that with a .05 level of significance, power = .80, ICC = .08, number of clusters = 25, cluster size = 8, *N* = 200, we may be able to detect effect sizes of .49 (about medium effects according to (Cohen, 1988). We recruited 30 course leaders rather than 25 and we can withstand a total waiver of five of the groups while still identifying the effect size we have calculated.

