Date of first enrolment	01/11/2015
Target sample size	35 clusters with 8–12 adolescents within each cluster
Recruitment status	Recruiting
Primary outcome(s)	1. Center for Epidemiological Studies Depression Scale, CES-D for adolescents, at Pre-test, T1, T2, T3, T4
	2. Dysfunctional Attitudes Scale (DAS) (short version) at Pre-test, T2, T3, T4
	3. Automatic Thoughts Questionnaire (ATQ) (short version) at Pre-test, T2, T3, T4
	4. Ruminative Response Scale (RRS) (short version) at Pre-test, T2, T3, T4
	5. Emotion regulation at Pre-test, T2, T3, T4
	6. Dropout (from school and official registries) at T1, T2, T3, T4
	7. Grades at T1, T2, T3, T4
Key secondary outcomes	1. Intentions to quit school at Pre-test, T2, T3, T4
	2. Social and Cognitive Competence at Pre-test, T2, T3, T4
	3. Life events at Pre-test, T2, T3, T4

Course leaders were recruited from the Educational Psychological Services, School mental health offices, and so on. To become certified as an ACDC course leader, one must have completed a minimum 3–year college/university education before attending the 5 day certification course. The trainers are either doctors, psychologists, nurses, educators, social workers, occupational therapists or physiotherapists. All are employed in community health, public health/public hospitals, schools or in private healthcare.

The course leaders have been randomized to experimental and control conditions by administrative personnel at the Norwegian Center for Child Behavioral Development. The control groups of adolescents will receive practice as usual, so those course leaders will be offered their training shortly after the experimental groups have finished after 14 weeks. Our design is thereby a cluster randomized trial where groups (course leaders) rather than individuals are randomized.

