### Participants and recruitment

Approximately 8–12 adolescents of both genders are considered a preferred group size, and 30 groups will be recruited. The target population is students from the 1^st^ or 2^nd^ grade from upper secondary school, who are 16/17 years old. There is a maximum cut-off age of 20 years and subjects must have subclinical depression or mild to moderate depression, according to the criteria of the DSM. Inclusion will be evaluated through a semi-structured interview by the course instructor/control leader. Generally, the participants will be recruited through their general practitioner, the School Health Service, public health nurses, the Educational and Psychological Counselling Services (PPT) or the Children and Young People’s Psychiatric Out-patient Services (BUP). Exclusion criteria include presence of bipolar disorder, psychosis, substance-use, ADHD or ADD and brain damage as listed in the ACDC manual.

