### Study status

The intervention started in January 2016. Out of a total of 30 recruited course-leaders, only 19 was established due to difficulties in the recruitment process, and some with low cluster size. In order to fulfill the requirements following our power-calculations, more adolescents need to be recruited. Another training of course leaders will take place in the autumn of 2016, so that an additional intervention period can be executed. Recruitment procedures will be revised. The planned additional intervention will take place in the spring of 2017.

For the intervention in the spring of 2016, post-test assessments are scheduled to be completed by the end of June 2016.

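### The detectable effect of .49 ignores the small number of randomised clusters and any loss within groups, so the margin is two groups of 30, not five; Table 1's 35 clusters also disagrees with 30 elsewhere

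*Protocol article*

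**What the plan says.** The section on sample size and power calculations in the protocol article takes an ICC for depressive symptoms from an earlier study of the same course. It lists its inputs as "with a .05 level of significance, power = .80, ICC = .08, number of clusters = 25, cluster size = 8", giving N = 200, and concludes that "we may be able to detect effect sizes of .49". It adds that 30 course leaders were recruited, not 25, so that "we can withstand a total waiver of five of the groups while still identifying the effect size we have calculated".

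The section on participants and recruitment agrees with the 30: "30 groups will be recruited", with a preferred size of about 8 to 12. Table 1 (the registration data set) instead gives a target of "35 clusters with 8–12 adolescents within each cluster".

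The section on study status reports what happened in the first cohort: "Out of a total of 30 recruited course-leaders, only 19 was established", some of them small. It announces a second intervention period so that the requirement from the power calculation can be met.

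**The concern.** The calculation allows for clustering through a design effect, but its result matches a large-sample formula. When 25 clusters are randomised, the treatment comparison rests on 25 cluster-level units, and normal quantiles overstate the power. The statement about losing five groups then builds on that figure. It treats 25 groups of 8 as sufficient, with all 8 observed in each, although the statistical analysis section expects missing data and the 6- and 12-month follow-ups are collected by electronic link.

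Two things are at stake. A null result on depressive symptoms could be read as coming from a trial with 80% power for .49, when the stated design gives less. And the study status section uses this calculation as the requirement for the second cohort, so an optimistic requirement carries forward into recruitment. Separately, a reader cannot tell whether the target is 30 or 35 clusters.

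**Working it through.** **Inputs.** From the sample size section: 5% level, power .80, ICC .08, 25 clusters, 8 per cluster. The course leaders of the first cohort were split 15 and 15 (Design section), so near-equal arms are assumed: 12 and 13 clusters out of 25. Assumptions not stated in the article: two-sided test, equal cluster sizes, same ICC in both arms, no baseline adjustment.

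**Formulae.** Design effect DE = 1 + (m − 1) × ICC. Standard error of the standardised difference SE = √[DE/m × (1/k₁ + 1/k₂)], with k₁ and k₂ clusters per arm.

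**Step 1: reproduce the plan's figure.**
- DE = 1 + 7 × .08 = 1.56; effective N = 200/1.56 = 128.2.
- SE = √[1.56/8 × (1/12 + 1/13)] = .1768.
- Normal quantiles: (1.960 + 0.842) × .1768 = .495. Power at .49 is 79.2%.

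So .49 follows from its inputs by the usual large-sample method.

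**Step 2: use the cluster-level degrees of freedom.** With 25 clusters in two arms there are 25 − 2 = 23 degrees of freedom. The t quantiles are 2.069 and 0.858, and (2.069 + 0.858) × .1768 ≈ .517; the noncentral t gives the same. Power at .49 is 75.6%.

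**Step 3: how many groups of 8 does .49 need?**

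| Clusters of 8 | Detectable effect, normal | Detectable effect, t | Power at .49, t |
|---|---|---|---|
| 25 | .495 | .517 | 76% |
| 27 | .476 | .495 | 79% |
| 28 | .468 | .486 | 81% |
| 30 | .452 | .468 | 83% |
| 35 | .418 | .431 | 89% |

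The smallest number that reaches 80% power at .49 is 28, so 30 − 28 = 2 groups can be lost, not 5. If all five came from one arm (10 and 15 left), the t-based figure would be .527 and power at .49 would be 74%.

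**Step 4: loss within groups.** The article gives no rate, so 20% is assumed for illustration: 8 × .8 = 6.4 analysed per group, DE = 1 + 5.4 × .08 = 1.432.
- 25 clusters: SE = √[1.432/6.4 × (1/12 + 1/13)] = .1894. Detectable effect .531 by the normal method (power at .49 is 73.5%) and .554 by t (70%).
- All 30 clusters: .484 by the normal method and .501 by t (78%).

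With that loss, 25 groups fall short of .49 even by the method that produced it.

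**Step 5: cluster numbers side by side.** The sample size section reconciles 25 (required) with 30 (recruited, with reserve), and the recruitment section repeats 30. Only the 35 in Table 1 is unexplained. The choice matters: at size 8 it is .431 against .468.

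**The case against.** The strongest reply is that .49 is a fair approximation. It reproduces, clustering is included, the wording is cautious, and .52 is still about a medium effect. The calculation also takes no credit for two features of the plan. Size 8 is the bottom of the planned range: on the t basis, 25 groups of 10 detect .486 (81% power at .49) and 25 of 12 detect .464 (84%). Depressive symptoms are also measured before the course. If baseline explained 10% of outcome variance (an assumption), the t-based figure for 25 groups of 8 would be .491; at 25% it would be .448, or .480 with the 20% loss as well.

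Much of this stands. The t correction is worth about four percentage points of power, and larger groups or baseline adjustment could offset it. But the sample size section claims neither, it fixes size 8, and the study status section reports that some groups were small. The claim about five groups is made for the stated inputs, and for those it does not hold on the cluster-level basis.

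Three stronger readings are tempting, and the article does not support them.
- *That .49 is an arithmetic error.* It is the result of a standard approximation.
- *That there are three rival targets.* The 25 is the required minimum, and 30 − 5 = 25 is consistent.
- *That the 19 established groups leave the trial underpowered without saying so.* At 19 groups of 8 the t-based figure would be about .60, but the article discloses the shortfall (11 of 30, against an allowance of 5) and plans a second cohort. No analysis of 19 groups alone is put forward as the main result.

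**Conclusion.** The point holds and should be fixed. On 23 cluster-level degrees of freedom, the stated design detects about .52 and has about 76% power at .49, not 80%. The margin for lost groups of 8 is two, not five, and there is no allowance for adolescents lost within groups. This rests on a two-sided test, near-equal arms, equal group sizes and no baseline adjustment. The .55 (t) and .53 (normal) after individual loss rest on an assumed 20%, which the article does not give. The conflict between 35 and 30 clusters needs no assumption. The overall size is modest: three more clusters of 8 than the 25 stated, or none if analysed groups average 10.

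**What to change.** 1. In the sample size section, restate the detectable effect with a t reference on clusters minus 2 degrees of freedom: about .52 for 25 clusters of 8, or about .47 for all 30. If credit is taken for larger groups or for baseline adjustment, state the assumed size or correlation.
2. Replace the sentence about losing five groups. Either give a margin of two groups at a fully observed size of 8, or give the detectable effect after stated losses of groups and of adolescents.
3. Use the revised figures as the requirement that the study status section applies to the second cohort.
4. Reconcile the 35 clusters in Table 1 with the 30 in the text, and say whether the target counts recruited or established groups, over both cohorts.

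The cost is wording and a check of the registry entry. No design change follows, and the stated detectable effect becomes slightly less favourable.

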### Data management

Cases are labelled with 11-digit social security codes throughout the project period. Personally identifiable information is required to connect self-reported data with information from school and inquiries about grades and dropout. Pre-intervention data will be collected by trainers for groups, while follow-up studies after 6 and 12 months are collected directly from the Norwegian Center for Child Behavioral Development through the posting of link to an electronic questionnaire. The study will make use of two separated databases for storing research data and contact information. All participants will receive an ID number. Collected data will be stored in a research database. The data will be stored in a safe manner, where only employees at the center authorized by the research director has access. Contact information for young people, such as the social security number, participant’s name, phone number, email and address will be kept in a separate database, unrelated to the research database. Our supplier Confirmit buys physical capacity and locality in RackspaceUK outside London. The data will then be stored on servers at RackspaceUK. Rackspace UK is a subsidiary of Rackspace Inc in the United States. Rackspace Inc is Safe Harbor compliant. This can be verified through https://safeharbor.export.gov/list.aspx. The electronic data collection happens via email project done by questionnaires emitted from the contact database. When the questionnaire is answered, the information is sent to the research database. The databases are protected by two factor authentication, where both have a personal password and unique passwords used every time you log in. If adverse events occur, the course leaders will report to the project leader. More details are described in the application to the ethical committee.

### Statistical analysis

SPSS will be used for 1) descriptive analyses for each time point and 2) repeated measures General linear models (GLM) for estimation of intervention effects. Structural equation modelling (SEM) will be used for latent growth curve models (LGC) to investigate individual variations in level and change across time [62–64]. The LGC can be used for estimation of intervention effects by comparing intervention and control group data through multiple-group LGC. These results can be compared with results from GLM. The LGC can also be expanded to Latent growth mixture models to explore whether there are sub-groups of individuals constituting specific clusters with change patterns deviating from the average change pattern estimated by use of traditional LGC [65]. Predictors can be added to the trajectories. Missing data will be handled by the FIML procedure in Mplus (if MAR).

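### Course leaders are randomised and the power claim assumes a cluster-adjusted test, but the repeated-measures GLM named for estimating effects has no course-leader term

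*Protocol article*

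**What the plan says.** All places are in the protocol article.

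- Design section, on the unit of randomisation: "Our design is thereby a cluster randomized trial where groups (course leaders) rather than individuals are randomized".
- Sample size and power calculations: "possible cluster effects must be accounted for when calculating appropriate sample size". The ICC comes from the earlier ACDC study, with course groups as clusters: "ICC for depressive symptoms was .08". The calculation is set "with a .05 level of significance", with "power = .80, ICC = .08, number of clusters = 25, cluster size = 8" (N = 200), and concludes "we may be able to detect effect sizes of .49".
- Statistical analysis: SPSS is to be used for "repeated measures General linear models (GLM) for estimation of intervention effects". Intervention effects may also be estimated by "comparing intervention and control group data through multiple-group LGC", and the two sets of results may be compared.

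The Statistical analysis section mentions no course-leader effect, multilevel model, cluster-robust standard error or cluster-level analysis. Where it speaks of clusters, it means latent sub-groups of adolescents with similar trajectories, not course groups. No other section says that the effect analysis allows for course leader.

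**The concern.** The unit of randomisation, the power calculation and the effect analysis should agree, and the third does not match the first two. A standard repeated-measures GLM takes the adolescent as the independent unit. It handles the correlation between one adolescent's repeated scores, but not the correlation between adolescents who share a leader.

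If leader effects influence the tested contrast, the standard error is too small, the interval too narrow and the false-positive rate above the nominal 5%. This touches CES-D, a primary outcome and the one on which the trial was powered. The number of clusters is also modest: the Study status section reports that only 19 of 30 course leaders' groups were established in the first round. The degrees of freedom of a correct test would therefore be limited, whereas the GLM would use those of the adolescents.

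**Working it through.** **Inputs.** From the sample-size section: alpha .05 (sidedness not stated; two-sided assumed), power .80, ICC .08, 25 clusters of 8, N = 200. From the participants section: preferred group size 8–12. Equal allocation follows from the 15 and 15 leaders in the first round.

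**Step 1: reproduce the stated .49.**
- Design effect (DE) = 1 + (8 − 1) × .08 = 1.56.
- Effective N = 200 / 1.56 = 128.2.
- Detectable effect = (1.960 + 0.842) × √(4 / 128.2) = 0.495.
- Without clustering: (1.960 + 0.842) × √(4 / 200) = 0.396.

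The stated figure reproduces only with the design effect. The power claim therefore presupposes a cluster-adjusted test.

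**Step 2: an unadjusted post-test comparison of arms.** The true standard error is √DE times the one used, so type I error = 2 × [1 − Φ(1.96 / √DE)]. At ICC .08:

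| Per cluster | DE | √DE | True type I error |
|---|---|---|---|
| 4 | 1.24 | 1.11 | 7.8% |
| 5 | 1.32 | 1.15 | 8.8% |
| 8 | 1.56 | 1.25 | 11.7% |
| 10 | 1.72 | 1.31 | 13.5% |
| 12 | 1.88 | 1.37 | 15.3% |

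Simulation agrees: 11.6% for 24 clusters of 8, and 14.8% for 30 clusters of 12. A t-test on cluster means in the same data gave 4.8–5.1%.

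Sensitivity to an assumed ICC, at 8 per cluster: .02 gives 6.6%, .05 gives 9.2%, .10 gives 13.3%. If only the ACDC arm is clustered, the average DE is (1.56 + 1) / 2 = 1.28 and the rate is 8.3%.

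**Step 3: the arm-by-time test over the five CES-D occasions (T0–T4).** This depends on how leader effects change over time, which the article does not give. The simulations used 24 or 25 clusters of 8, ICC .08 and no true effect. Assumptions not taken from the article are a within-person correlation of .6 and, where leader effects arise after T1, a correlation of .8 between them over T2–T4.

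| Leader effects | Arm-by-time rejection at nominal 5% |
|---|---|
| None | about 5% |
| Constant over all occasions | about 5% |
| After T1, ACDC arm only | about 12% |
| After T1, both arms | about 16–17% |

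Repeat runs of the last row gave up to 18%, and a variant with similar settings gave 19.5%.

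**Step 4: the arm main effect in the same GLM.** With leader effects constant over time, where the arm-by-time test is safe, the test of the arm main effect rejected about 14% of the time.

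**The case against.** Four arguments deserve a fair hearing.

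1. *A condensed article leaves detail to the analysis plan.* This holds for the LGC. The section says only that it can be used for effects, and it names Mplus, which can fit two-level models or give cluster-robust errors. A reader might infer that both analyses treat adolescents as independent; the text does not support that for the LGC. It does not rescue the GLM, which is a specific named method that does not fit the design rather than an unstated setting.

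2. *The arm-by-time test removes leader effects that are constant over time.* This is correct, and the sample-size section does not say whether .08 refers to level or to change. So it cannot be said that p-values will be too small in every case. However, a course delivered in groups makes leader effects that arise after the start plausible, and constant effects inflate the arm main effect instead.

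3. *Clustering may be weaker than assumed.* The ICC comes from ACDC groups, whereas control adolescents receive usual care, which may be no treatment. The Study status section also reports some small clusters. Both lower the inflation, as the 8.3% figure and the rows for 4 and 5 per cluster show. A flat statement that the error rate is two to three times nominal is therefore not supported.

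4. *A clear result would survive.* A reader might conclude that no positive CES-D finding could be believed. That goes too far. With DE 1.56, an unadjusted p below about .014 remains significant at .05 (1.96 × 1.249 = 2.45), and at an effect of .49 with N = 200 the expected unadjusted z is .49 / √(4 / 200) = 3.5.

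**Conclusion.** The point holds for the repeated-measures GLM: the power calculation assumes a cluster-adjusted test, and the analysis named to deliver it does not adjust. For the LGC, the handling of clusters is unspecified rather than wrong.

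The direction of the error is certain whenever leader effects enter the tested contrast; its size is not. For a post-test comparison at ICC .08 with both arms clustered, true type I error is about 8–9% at 4–5 per cluster, 11.7% at 8 and 15% at 12. For arm by time, the range is about 5% to 16–17%. The arm-by-time figures rest on the assumed correlations above, and all figures rest on a two-sided test. The correction should be made before the effect analysis is run, because the analysis concerns a primary outcome and the change is small.

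**What to change.** In the Statistical analysis section, replace the repeated-measures GLM as the effect analysis with a linear mixed model that has random effects for course leader and for adolescent, and Satterthwaite or Kenward–Roger degrees of freedom. State that any LGC used to estimate effects takes course leader as the cluster, by a two-level model or cluster-robust errors. It would also help to say whether the ICC of .08 refers to level or to change.

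A separate leader variance in each arm and a leader-level permutation test are useful checks but optional.

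The cost is a rewritten paragraph, modest analysis work and wider intervals. With 25 clusters and 25 − 2 = 23 degrees of freedom, the detectable effect becomes 0.517 rather than 0.495. No new measurements are needed, but the leader or group identifier must be kept in the research database. The Data management section describes participant identifiers and does not say that a leader code is stored, so this should be written down rather than assumed.

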#### Primary outcome measures

Dropout will be measured from school reports.

The level of depressive symptoms as assessed by the Center for Epidemiologic Studies Depression Scale for adolescents (CES-D; [44]) will also serve as one of the primary study outcomes. CES-D asks for the frequency of symptoms during the last week of depressed affect (7 items), lack of positive affect (4 items), somatic and retarded activity (7 items), and interpersonal problems (2 items). A four-point Likert scale is used (total score range: 0–60). A previous confirmatory factor analysis supported the use of four dimensions invariantly to gender and differing ethnic backgrounds in Norway [45].

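### The SPSS repeated-measures GLM, the committed analysis of the intervention effect, has no missing-data method; FIML covers only the Mplus models

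*Protocol article*

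**What the plan says.** The Statistical analysis section assigns SPSS to "repeated measures General linear models (GLM) for estimation of intervention effects". This is stated as something that will be done. The latent growth curve (LGC) model is planned firmly for individual variation in level and change, but for the treatment effect it is only an option: "The LGC can be used for estimation of intervention effects by comparing intervention and control group data through multiple-group LGC". The section then adds: "These results can be compared with results from GLM".

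The one sentence on missing data is "Missing data will be handled by the FIML procedure in Mplus (if MAR". No imputation or other handling is stated for the SPSS analysis.

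Three other places bear on the point:

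- **Number of waves.** Table 1 lists the depression outcome as "Center for Epidemiological Studies Depression Scale, CES-D for adolescents, at Pre-test, T1, T2, T3, T4", and Table 2 shows the same five occasions.
- **Mode of follow-up.** Under Data management, the trainers gather the pre-intervention data. The later waves reach the study by another route: "follow-up studies after 6 and 12 months are collected directly from the Norwegian Center for Child Behavioral Development through the posting of link". That link opens an online form.
- **School dropout.** Under Primary outcome measures, "Dropout will be measured from school reports". Table 1 adds official registries.

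**The concern.** The missing-data method is attached to the model that is optional for the treatment effect, and the model that is committed for it has none. A repeated-measures GLM in SPSS takes one row per person and needs every entered wave. Unless values are imputed first, a person with one gap is lost from the whole analysis. FIML keeps everyone with at least one observed wave.

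Three things are at stake:

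1. **Precision.** CES-D is measured five times, so losses compound across waves. The power calculation counts 200 adolescents and allows only for the loss of whole groups.
2. **Validity.** FIML is valid when missingness depends on observed data. A complete-case analysis generally needs a stronger condition. In a trial of depressed adolescents, non-response at T3 and T4 could well follow earlier CES-D scores.
3. **Interpretation.** If the GLM and LGC estimates differ, the reader cannot tell whether the model or the set of adolescents caused it.

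**Working it through.** **Inputs from the article** (Sample size and power calculations): two-sided reading of alpha .05, power .80, ICC .08, 25 clusters of 8, N = 200, detectable effect .49. The article states no rate of missed waves, so every loss rate below is an assumption.

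**Step 1. Reproduce the stated figure.**
- Design effect = 1 + (8 − 1) × .08 = 1.56.
- Standard error of the standardised difference = √(4 × 1.56 / 200) = .177.
- Detectable effect = (1.960 + .842) × .177 = .495.
- Power at .49 = Φ(.49/.177 − 1.960) = 79%.

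The two-sided normal approximation therefore matches the article's .49 and .80, but only with 200 complete adolescents.

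**Step 2. Complete cases under an assumed loss.** With loss q per wave, independent over w waves, the complete fraction is (1 − q)^w. The same formulae apply with cluster size 8 × (1 − q)^w.

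| Assumed loss per wave | Waves that can be missed | Complete of 200 | Detectable effect | Power at .49 |
|---|---|---|---|---|
| none | – | 200 | .495 | 79% |
| 5% | T2–T4 | 171 | .519 | 75% |
| 10% | T2–T4 | 146 | .546 | 71% |
| 10% | T1–T4 | 131 | .566 | 68% |
| 20% | T2–T4 | 102 | .618 | 60% |

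For the 131 row: .9⁴ = .656; cluster size 8 × .656 = 5.25; design effect 1 + 4.25 × .08 = 1.34; standard error √(4 × 1.34 / 131) = .202; detectable effect 2.802 × .202 = .566; power Φ(.49/.202 − 1.960) = 68%.

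**Step 3. Does selection bias the estimate?** This was examined in a small simulation built on assumptions only: five waves with correlation .6, 100 adolescents per arm, a true effect of −.49 from T2 on, no clustering, and permanent loss from T2 on that depends on the previous score. About 60–64% were complete. The T4 effect estimates were:

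| Missingness depends on previous score | Complete cases | FIML-type estimate |
|---|---|---|
| not at all | −.49 | −.49 |
| equally in both arms | −.46 | −.49 |
| in control only, moderate | −.31 | −.49 |
| in control only, stronger | −.23 | −.49 (−.485) |
| in intervention only | −.65 | −.49 |

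Dependence that is equal in the two arms moves the complete-case estimate little. Dependence that differs by arm moves it a good deal, and in either direction.

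**The case against.** **A condensed article leaves detail to an analysis plan.** Which waves enter the GLM, and whether imputation precedes it, could be settled there. Deletion of incomplete cases is a property of the procedure, not something the article states. This is fair as far as it goes, and imputing before the GLM would remove the mismatch. But the article does name the software, the models and the missing-data method, and those parts do not fit together. That is more than an omitted detail.

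**A reader might infer that the GLM excludes the adolescents most at risk of leaving school.** The article does not support that. The Background links mental health to school dropout, but nothing links either to missed questionnaires. The centre sends the T3 and T4 link itself and holds phone, email and address, so leaving school does not break contact. Nor is the school-dropout outcome lost with a missed questionnaire, because it comes from school reports and registries.

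**The size could be overstated.**
- A t distribution on 23 df gives .59 and 64% with 131 complete. It already gives .517 and 76% with nobody missing, so setting .59 and 64% against the article's .49 and 80% would mix two effects.
- Independent loss is pessimistic. If the same 10% missed every wave, 90% would remain.
- Table 1 targets 35 clusters of 8–12, that is 280–420 adolescents. From 280, the same 10% loss leaves 204 (T2–T4) or 184 (T1–T4). Against this, Study status reports that only 19 of 30 course leaders were established, with a second cohort planned.
- Some precision is lost under FIML too.

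All four qualifications stand, and the figures are given as illustration only. The absence of a sensitivity analysis for data not missing at random is ordinary analysis-plan content and is not part of this point.

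**Conclusion.** The point holds in a limited form. The committed estimator of the CES-D effect has no stated missing-data method and, with no imputation stated, would run on adolescents complete for all entered waves. The optional estimator would use everyone with at least one wave. Two consequences follow whenever waves are missed: the GLM loses precision, and any difference between GLM and LGC mixes model with sample. Bias is possible but not established. It depends on whether non-response follows earlier CES-D and mainly on whether that differs by arm, and the article says neither.

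For scale, an assumed independent 10% loss at T1–T4 costs about 11 percentage points of power at .49 (79% to 68%) and raises the detectable effect from about .495 to .57. Limiting the loss to T2–T4 gives 71% and .546. Overlapping non-response would make the cost smaller. This should be changed, because it weakens the estimate the trial relies on and is cheap to repair.

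**What to change.** Name one likelihood-based model that accounts for course-leader clusters and uses every available CES-D wave as the primary estimate of the CES-D effect. Either a mixed model or the growth model in Mplus with clustering and FIML would serve. Drop the repeated-measures GLM, or keep it labelled as a complete-case sensitivity analysis, so that a difference from the primary result is read as reflecting sample as well as model.

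To make the missing-at-random assumption more credible, include T0 CES-D, screening BDI, and school-reported grades and dropout as auxiliary variables. Use absence only if it comes from school records: Table 2 lists it among the administered measures, so it may be missing for the very adolescents who do not respond.

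The cost is analysis wording and a little programming. No new data collection is needed.
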